#### Control condition: first dose of control task is guided with researcher support (Day 1)

2.5.4

As per the intervention condition, the first session will be guided remotely by a trained researcher. Participants in the control condition will be instructed to listen to a podcast with neutral content about theoretical aspects of philosophy (the episode ‘Vägen till en svensk filosofi’ of the podcast ‘Filosofiska Rummet’ [30], accessed either by clicking on a link in the electronic platform or by inserting www.sverigesradio.se/avsnitt/1073596 in the web browser of their smartphone) for at least 20 min. They will watch a video of a researcher describing the task (0:53 min), i.e., to listen uninterrupted to the podcast for at least 20 min and focus on what is being said. Participants will be told that they can continue listen to the episode on their own later on. They will then receive information about how to access the podcast audio file. The researcher will provide support as needed and will monitor the time while the participant is listening to the podcast. This comparator was chosen based on pilot work [25] and is intended to match the intervention condition for attention demands, expectation effects, delivery device (smartphone), time spent with the researcher, as well as the need to navigate the blended digital materials (electronic platform and links to external websites) in this remote setup.

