#### Intervention condition: first dose of the intervention is guided with researcher support (Day 1)

2.5.3

The first intervention session will be guided remotely by a trained researcher and includes the following three components: (1) A **brief memory reminder cue**; (2) engaging in a **visuospatial interference task for at least 20 min**; and (3) actively **using ‘mental rotation’** during the gameplay.

First, participants will be given information about the intervention and how it should be carried out (video of a researcher, 1:51 min, researcher available for questions/clarifications). They will be informed that the target image of the traumatic event needs to be active in memory before gameplay, and that they need to play the game in a particular way (i.e., using mental rotation).

*List of intrusive memories – memory reminder cue procedure.* Then, participants will watch a video of a researcher (2:03 min) explaining how to complete a list of their intrusive memories which involves briefly describing ‘what they see’ when they experience each intrusive memory. This element will be guided by a researcher who will also ask the participant to write a brief description of each memory (e.g., ‘face of a patient who cannot breathe’) into the electronic data collection platform, one image at a time until each intrusive memory has been described. At no stage will participants be asked to describe the trauma in detail. Participants will then be asked to choose one intrusive memory from their list and gently bring that target image to mind; i.e., focus briefly on one intrusive image so that it becomes active in working memory as a visual mental image.

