*Tetris gameplay with mental rotation and recap.* After this memory reminder cue procedure, participants will watch an animated video explaining how to play Tetris using mental rotation (2:43 min, accessed via a link in the electronic platform leading to an external website where the video is stored). They will then access the game Tetris® (either by clicking on a link in the electronic platform or by inserting www.tetris.com in the web browser of their smartphone), skipping any advertisement that comes up in this free version of Tetris, and adjusting the settings to ‘ghost piece off' (c. 2–3 min). Participants will then be encouraged to play the game for at least 20 min, whilst actively using ‘mental rotation’ throughout the gameplay, i.e., planning ahead and visualizing in their mind's eye how to rotate and move upcoming Tetris blocks to fit them into a horizontal line. During gameplay, the researcher will provide support as needed and monitor the time spent playing.

After gameplay, participants will watch a final animated video (1:37 min, accessed via a link in the electronic platform leading to an external website where the video is stored) which re-caps the procedure and includes an illustration of what is happening in the brain [29] during the task. This information is included to provide participants with a re-cap on what they have done during the session and - in keeping with the approach of established psychological interventions (e.g., cognitive behaviour therapy) - to provide participants with a rationale for the intervention, and some brief information about the hypothesized mechanisms. Further, the video re-emphasizes that it is important to use mental rotation when playing Tetris, as mental rotation can be one of the more difficult aspects of the gameplay instructions to grasp. That is, participants are reminded that they should imagine the upcoming blocks in their mind's eye (rather than just focus on the single block entering the game and simply swiping as they might usually do). The video highlights where in the brain the process of mental rotation happens. Overall, this last video aims to help participants remember the rationale for and components of the intervention that they can use later in a self-administered booster.

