*Explanation of booster sessions for persistent intrusions or for different intrusions on the list.* After the first ‘dose’, the intervention can be repeated independently for the remaining intrusive memories on the participant's list, and/or if the targeted memory were to persist. Thus, in this last phase of the guided session, the researcher will explain how to use the intervention in a self-administered way; e.g., encourage participants to use it after they experience an intrusive memory in daily life (i.e., when an image comes to mind involuntarily) if it is convenient to do so. It may be the case that in many instances, it is not feasible for participants to use the intervention immediately after experiencing an intrusion (e.g., if they are at work). Accordingly, another option for participants who experience persistent intrusions would be for them to find a more convenient time when they can *deliberately* bring the intrusive image to mind (via the memory reminder cue procedure). Whether the memory is involuntarily or deliberately retrieved, participants will be encouraged to next play Tetris with active mental rotation for at least 20 min continuously. They are not expected to do the task procedure each and every time they have an intrusion, rather it is participants' choice as to how they can flexibly fit boosters into their daily life. We also note that the intervention is to be conducted once for each different intrusive memory (i.e., from participants' *list of intrusive memories*) – thus if the same memory intruded 10 times, the booster would be done once. However, if two different memories intruded, two boosters would be needed. If a given memory continues to persist, then a booster could be done again. Participants can also receive researcher-guided ‘Booster doses’ (i.e., with remote researcher support, see 2.6.5).

*Duration of the intervention.* The guided intervention task procedure conducted with researcher support will be approximately 25 min in duration; when self-administered the intervention takes c. 20 min.

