#### Booster procedures

2.5.5

Participants in both conditions will be informed that they can contact the research team at any time during the study; thus, will have the option to e.g., ask the research team for researcher-guidance, including advice about the repeated use of the task procedure, or to ask any other questions they may have about the study procedures. In the first researcher-guided session, participants in both conditions will be informed that they can repeat the task procedure on their own (i.e., option for self-administered booster doses).

Participants in both conditions will be asked to monitor the number of intrusions they experience in the week following the first session (i.e., Week 1 diary) and can receive reminders from the research team if they stop filling in the diary (see 2.6.6).

As described above (see 2.6.3), participants in the intervention condition will be encouraged to repeat the intervention if they experience persistent intrusive memories. They could do this in two ways – either (a) use the gameplay task procedure directly after experiencing an intrusion, or (b) as the former is not always practical in daily life, they could set aside a time to do the intervention by deliberately recalling the specific memory that is persistent (i.e., gently bring to mind the image that had intruded) and then complete the gameplay task procedure. Monitoring of intrusive memories in the diary is a means by which the participant can notice whether a booster session may be useful.

Participants in the control condition will not be given instructions to repeat the task if they experience an intrusive memory. On balance, we did not consider it justified at this stage in the research to (after a first session) ask healthcare staff during the pandemic to engage in a task hypothesized to be non-active but potentially time consuming.

For participants in the intervention group only, ‘boosters’ (self-administered or researcher-guided) can be initiated by the research team. Researchers will monitor incoming diary data in the intervention condition during Week 1. In the event that a participant continues to report persistent intrusive memories after the initial intervention session, the researcher will contact the participant to:1)ask them if the intrusion/s was/were from the most recently targeted image (i.e., the image selected in the first guided sessions with the researcher or in a self-administered booster); or a non-targeted image.

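### The control is said to match expectation and researcher time, but the described procedures match neither, so a Week 5 difference belongs to the whole intervention package and not to the cognitive task alone

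*Protocol article*

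**What the plan says.** The comparator is described in section 2.5.4 as "intended to match the intervention condition for attention demands, expectation effects, delivery device (smartphone), time spent with the researcher", together with the need to navigate the same digital materials. Section 2.5.2 adds that the researcher aims to stay on the call for the whole first session in either arm.

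For the intervention arm, section 2.5.3 lists four task videos, starting with an introduction ("video of a researcher, 1:51 min, researcher available for questions/clarifications"). It also lists a researcher-guided list of intrusive memories, game set-up, at least 20 min of play and a researcher's explanation of later boosters. The fourth video comes after play and is there in part "to provide participants with a rationale for the intervention, and some brief information about the hypothesized mechanisms". On length, the section says: "The guided intervention task procedure conducted with researcher support will be approximately 25 min in duration".

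For the control arm, section 2.5.4 describes one task video ("They will watch a video of a researcher describing the task (0:53 min"), help with opening the podcast and at least 20 min of listening. It describes no rationale or mechanism video.

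For Week 1, section 2.5.5 says: "Researchers will monitor incoming diary data in the intervention condition during Week 1". If intrusions persist, the researcher contacts the participant. That section reserves team-initiated boosters for the intervention group. Controls are told they may repeat the task but are not instructed to, and the stated reason is the burden on staff of a task thought to be inactive.

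**The concern.** The claimed match is what would let a reader treat a difference between arms as an effect of the cognitive task over and above attention and expectation. The primary outcome (section 3.1) is a self-reported diary count, which can plausibly respond to both. If one arm gets more researcher time, an explanation of why the task should work, and follow-up contact when symptoms persist, the comparator does not hold those factors constant. The primary hypothesis (section 2.1.1) labels the comparator an attention placebo control, which invites attribution to the task itself. The measure that might reveal an imbalance in expectation, the credibility/expectancy questionnaire (section 3.3.4.2), is completed before the task. It therefore precedes the rationale video and every booster contact.

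**Working it through.** **Inputs.** Video lengths, set-up time and minimum task time come from sections 2.5.3 and 2.5.4. Booster contents come from section 2.5.5.

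**The plan's own figure of about 25 min.** Play of 20 min plus set-up of 2–3 min gives 22–23 min. That leaves 2–3 min for the memory cue, so about 25 min is reproduced if the videos are left out. With the videos included it is not reproduced, as the next step shows.

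**Day 1, intervention arm.**
- Videos: 1:51 + 2:03 + 2:43 + 1:37 = 8:14.
- Videos + set-up (2–3 min) + play (at least 20 min) = 30:14 to 31:14.
- Not timed in the document: writing the memory list and the booster explanation.

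**Day 1, control arm.**
- Video + listening: 0:53 + 20:00 = 20:53.
- Not timed: help with opening the podcast.

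**Day 1 difference.**
- Task videos alone: 8:14 − 0:53 = 7:21.
- All timed components: 30:14 − 20:53 = 9:21, up to 31:14 − 20:53 = 10:21. This counts set-up in one arm and no access time in the other.

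**Week 1, contact triggered by persistent intrusions.**
- Intervention arm with one call of about 15 min: 30–31 + 15 = about 45–46 min in total.
- Intervention arm with one full repeat (at least 20 min of play): at least about 50–51 min in total.
- Control arm: no counterpart is described.

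**Expectation, in time order.** Credibility rating (both arms), then task, then rationale video (intervention only), then Week 1 contacts over persistent intrusions (intervention only), then the Week 5 diary. No expectancy rating is described after the point where the arms diverge.

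**What the imbalance could do (assumption, not a finding).** The documents give no size for a contact or expectancy effect. Suppose the task were inert and these factors alone shifted the outcome by b standard deviations. Take the 65 completers per arm from section 4.2 and a two-sided 5% test. That 65 reproduces: d = (2.89 − 0.28)/√[(0.57² + 6.43²)/2] = 0.572, and 2(1.960 + 1.282)²/0.57² = 64.7, rounded up to 65. The chance of a significant result favouring the intervention is Φ(b√(65/2) − 1.96):

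| b (SD, assumed) | b√(65/2) | probability |
|---|---|---|
| 0.1 | 0.57 | 0.08 |
| 0.2 | 1.14 | 0.21 |
| 0.3 | 1.71 | 0.40 |
| 0.4 | 2.28 | 0.63 |

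The result is driven entirely by b, and a normal approximation is rough for skewed counts.

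**The case against.** The strongest reply is that the asymmetry is deliberate and open. Section 2.5.5 states that team-initiated boosters are for the intervention group only and gives a burden reason. The matching sentence says only what was intended and sits in the Day 1 section, so the Week 1 contacts do not strictly contradict it. Boosters are part of the intervention as defined, and the Discussion already ties interpretation to this guided, blended version. All of this stands. It does not rescue the matching sentence, because researcher time and rationale already differ on Day 1. The burden argument explains why controls are not asked to repeat the podcast. It does not reconcile the difference with the claimed match.

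Several stronger readings are tempting but not supported:
- **That the trial cannot support a causal conclusion.** It can, for the package as randomised. Only the separation of the task from contact and expectancy is lost.
- **That only the intervention arm gets researcher contact.** Both arms may call the team, and both may be contacted if diary entries stop (sections 2.5.5 and 2.5.6). Only contact prompted by persistent intrusions is one-sided.
- **That the contact trigger biases reporting of the primary outcome.** The trigger is the Week 1 diary, a secondary outcome, while the primary outcome is Days 29–35. Carry-over to Week 5, and its direction, is not shown.
- **That the intervention session is a known 45–50% longer.** That ratio (9:21 to 10:21 over 20:53) gives the control no access time and ignores quizzes and ratings common to both arms. The untimed memory list and booster explanation push the other way.
- **That the 25 min is an error.** It may exclude the videos, but the text does not say.
- **That the false-positive rate is about 21%.** That is one row of an assumption-driven table.

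**Conclusion.** The concern holds in a limited form. The protocol claims a match on expectation effects and researcher time that its own procedures do not provide, even within the first session. The firm figures are 8:14 against 0:53 of task video, and about 30–31 min of timed components against about 21 min plus untimed access help. A Day 1 gap exists, but its exact size is not established. Week 1 adds possible calls or repeat sessions in one arm only, and the pre-task credibility rating cannot show whether expectation stayed matched.

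A difference in the Week 5 count would be valid evidence about the task together with its rationale and researcher-initiated boosters, compared with one attention session. It would not be evidence about the cognitive task apart from contact and expectancy. How much these factors contribute cannot be derived from the document. The 8% to 63% range for 0.1 to 0.4 SD only shows that the answer depends on the assumption.

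**What to change.** 1. In section 2.5.4, limit the matching statement to what is matched: delivery device, minimum task time, one guided session and use of the digital platform. State that the contrast, and any conclusion drawn from it, concerns the intervention package (including the rationale and researcher-initiated boosters) versus a single attention session.
2. Log the number and minutes of researcher contacts in both arms and report them beside the primary result. Section 3.3.4.6 already records the number and dates of researcher-delivered boosters; minutes and control-arm contacts are not mentioned.
3. State whether the 25 min in section 2.5.3 includes the videos, and reconcile it with the component times.

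New check-in messages to controls are not recommended. Recruitment is under way, so they would make the control arm heterogeneous. They also would not equalise calls or full repeat sessions.

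The cost is a narrower claim, some rewording and a simple contact log. For participants already through the study, minutes may be unavailable, and the report should say so.

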#### Booster procedures

2.5.5

Participants in both conditions will be informed that they can contact the research team at any time during the study; thus, will have the option to e.g., ask the research team for researcher-guidance, including advice about the repeated use of the task procedure, or to ask any other questions they may have about the study procedures. In the first researcher-guided session, participants in both conditions will be informed that they can repeat the task procedure on their own (i.e., option for self-administered booster doses).

Participants in both conditions will be asked to monitor the number of intrusions they experience in the week following the first session (i.e., Week 1 diary) and can receive reminders from the research team if they stop filling in the diary (see 2.6.6).

As described above (see 2.6.3), participants in the intervention condition will be encouraged to repeat the intervention if they experience persistent intrusive memories. They could do this in two ways – either (a) use the gameplay task procedure directly after experiencing an intrusion, or (b) as the former is not always practical in daily life, they could set aside a time to do the intervention by deliberately recalling the specific memory that is persistent (i.e., gently bring to mind the image that had intruded) and then complete the gameplay task procedure. Monitoring of intrusive memories in the diary is a means by which the participant can notice whether a booster session may be useful.

Participants in the control condition will not be given instructions to repeat the task if they experience an intrusive memory. On balance, we did not consider it justified at this stage in the research to (after a first session) ask healthcare staff during the pandemic to engage in a task hypothesized to be non-active but potentially time consuming.

For participants in the intervention group only, ‘boosters’ (self-administered or researcher-guided) can be initiated by the research team. Researchers will monitor incoming diary data in the intervention condition during Week 1. In the event that a participant continues to report persistent intrusive memories after the initial intervention session, the researcher will contact the participant to:1)ask them if the intrusion/s was/were from the most recently targeted image (i.e., the image selected in the first guided sessions with the researcher or in a self-administered booster); or a non-targeted image.

If it was a non-targeted image, the researcher will: 2) encourage the participant to use the intervention on their own as soon as possible for this and all remaining non-targeted images (i.e., ‘SMS contact’, see below).

If it was a targeted image, the researcher will: 3) either offer the participant a ‘Full researcher-guided booster’, ‘Phone contact’, or ‘SMS contact’ (see below for more details).

In the current trial, we distinguish between three different types of ‘booster’ approaches:1)‘Full researcher-guided booster’ - phone contact between participant and researcher during which the full intervention procedure from Day 1 is repeated, i.e., bringing the target image to mind and at least 20 min of gameplay with mental rotation.2)‘Phone contact with researcher’ - phone contact between participant and researcher during which they together explore any difficulties/problem-solve around things that might have made the intervention/booster less effective (e.g., the intrusive image was not clear enough in the mind's eye before the gameplay task; the intrusive memory was not one image but consisted of several discrete visual images and needs to be repeated for each of those; how to engage in mental rotation). After exploring corrective information, the call will end (e.g., after approx. 15 min) and the participant can repeat the intervention procedure self-guided at another time convenient to them.3)‘SMS contact with researcher’- a brief SMS from the researcher encouraging the participant to do a self-administered booster dose (without researcher guidance) for any images that still intrude, one image at a time and practical information about how to repeat the intervention (e.g., how to access the game; timings).

#### Both conditions: completion of daily diary (Week 1 and 5) and follow-ups

2.5.6

Participants in both conditions will be asked to complete an intrusive memory diary and monitor the occurrence of any intrusive memories each day during Week 1 (secondary outcome) and Week 5 post-intervention (primary outcome). Participants will be asked to record the number of intrusive memories they experience each day during the week and to record zero if they did not experience any intrusions. The diary in the electronic platform is accessed via a link received by SMS or email (see 3.1).

Once they have completed the diary for each monitoring period (i.e., on the 7th day of each diary week), participants will be asked to provide overall ratings of intrusion vividness, intrusion-related distress and the extent to which intrusive memories affected their concentration during the past week. They will also be asked how many days, as well as nightshifts, they have worked during the previous week. Additionally, at the end of the Week 5 diary, participants will be asked if they can give an example of (a) how a specific intrusive memory has had a negative impact on their functioning, and (b) if a specific intrusive memory has reduced in number, how this has had a positive impact on their functioning.

Incoming diary data will be monitored by a researcher approximately once a day. Participants in both conditions will be contacted as necessary (e.g., if they cease to complete the digital diary to provide support regarding how to use it).

Participants in both conditions will complete secondary and other outcome measures and note the occurrence of any adverse events on day 7 (1-week). Follow-up measures will also be administered at 1-month, 3-months, and 6-months post-intervention. Data will be collected remotely/digitally (e.g., computer or smartphone) via a secure platform (i.e., SMART-TRIAL [28]). To promote participant retention and data collection, we will be flexible regarding the mode of collection of outcome measures (i.e., we include the option to collect them via telephone, SMS, or on paper if necessary), guided by participant preference.

Approximately a week after completing the primary outcome, participants in the intervention condition will receive a feedback letter thanking them for their participation and including a summary of the number of intrusions they reported at Week 0, Week 1 and Week 5. The letter will also remind participants that they can continue using the intervention if they experience intrusive memories, will include a brief note about the upcoming follow-up assessments, and inform participants that they can contact the research team if they would like to read the publication resulting from the study. Participants in the control condition will receive a similar feedback letter but without their intrusion data or a reminder to continue to use the task. Following an ethics amendment part way through the study, all participants will also be offered a voucher to reimburse them for their time and participation in the weeks after completing the primary outcome. At the end of the study, participants in both groups will also receive a standard letter to again thank them for their participation and provide them with information about publicly available mental health resources, should they wish to seek support.

